#### 2.5.7. Time Window

The indices of blood routine, blood biochemistry, and routine urine will be considered valid when measured in the first 7 days before the baseline period; 14 ± 3 d is acceptable for the measurements to be taken every 2 weeks during the treatment period, while 28 ± 5 d is acceptable for the measurements to be taken every 4 weeks during the follow-up period.

#### 2.5.8. Drug Quality Control

The JKYL medicinal (treatment and placebo) ingredients will be received from the same place of origin and the same season of the year. They will be purchased in full quantity and reserved after a quality inspection. The preparation methods for both groups' medicines shall be the same.

#### 2.5.9. Timeline

Recruitment began in September 2019 and is expected to end by December 2021. Table 2 provides a research timetable for registration, intervention, and evaluation.

#### 2.5.10. Data Collection and Management

After the test scheme is determined, a professional statistician shall be responsible for formulating the statistical analysis plan in consultation with the principal researchers using SAS statistical software and the data network platform designed by Jiangsu Famous Medical Technology Co. Ltd. Data Management Center.

#### 2.5.11. Statistical Analysis

The data analysis will be performed using SAS software (version 9.2). We will describe the data by using frequency counts and proportions (prevalence) for qualitative variables and means. Standard deviation (SD) will be used for normally distributed quantitative variables, while median and interquartile range (Q1 and Q3) will be used for nonnormally distributed quantitative variables. We will apply the chi-square test to examine the differences between the experimental and control groups for qualitative variables, the *t*-test to examine the differences between two groups for normally distributed quantitative variables (the homogeneity of variance will be tested between groups, and the Satterthwaite approximation will be used to correct the variance when the variance is uneven), and the Wilcoxon rank-sum test for nonnormally distributed quantitative variables. A generalized linear model will be applied for quantitative variables with repeated measures. In this study, *p* values < 0.05 (two-tailed) will be considered statistically significant.

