## 2. Methods and Analysis

### 2.1. Study Design

This will be a multicenter randomized double-blind placebo-controlled clinical trial. It will aim to objectively standardize the evaluation of the clinical efficacy, safety, and recurrence of blood-heat syndrome of psoriasis vulgaris treated with HCBC in CM. The results will be helpful for establishing the clinical standard of traditional CM in the treatment of psoriasis. The trial has been registered at NCT03961230. The start and end of recruitment was planned for January 2019 and December 2021, respectively.

Prior to the commencement of the study, the investigators and researchers require uniform training to ensure that the medical staff involved in the study are fully aware of all aspects of the trial. This study will be performed in five centers in China: Yueyang Integrated Traditional Chinese and Western Medicine Hospital, Beijing Traditional Chinese Medicine Hospital, First Affiliated Hospital of Anhui University of Traditional Chinese Medicine, Affiliated Hospital of Gansu University of Traditional Chinese Medicine, and Guangxi Zhuang Autonomous Region Institute of Dermatology Prevention and Control. Competitive enrollment will be applied in all research centers to achieve the goal of 196 total participants. Each participant can be enrolled only once.

Five phases will be included in the study: screening/registration, allocation, treatment/intervention, end of the intervention, and follow-up. During the initial screening, participants will be recruited through dermatology clinics, where they will undergo a physical examination and eligibility assessment. According to the assessment results, a run-in period of up to one week will be required. All patients who are diagnosed with psoriasis with blood-heat syndrome will undergo laboratory blood testing, including a complete blood cell count, liver function test, renal function test, and a pregnancy test before study inclusion. Additionally, routine urine tests, vital sign monitoring, and physical examinations will be performed (Figure 1). Patients who are willing to join the clinical trial will receive study information and consent forms. The consent forms must be signed before a patient will be included in this study.

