### 2.5. Outcome Measures

#### 2.5.1. Primary Outcome

The primary outcome is the reduction in the Psoriasis Area Severity Index (PASI) score, which will be calculated as follows: PASI reduction = (PASI at baseline)–(PASI at week 8 of the treatment period).

The PASI score of the patients will be assessed every 2 weeks during the treatment period and every 4 weeks during the follow-up period. The main result of the RCT will be the percentage of patients whose PASI score decreased by more than 75% compared with the baseline at 8 weeks [2].

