#### 2.5.4. Randomization, Allocation, and Blinding

This study will use central district stratification and block randomization. Random sequences will be generated by statistician researchers (implemented by the data Management Center of Jiangsu Famous Medical Technology Co. Ltd.). Eligible patients will be randomly assigned, in a 1 : 1 ratio, to one of the two groups (JYKL group or control group), aiming to balance baseline characteristics between the groups.

Throughout the study, participants, subjects, and study monitors will be blinded. Research drug random coding will be the only information linked to the group allocations. The random code will be maintained by Jiangsu Famous Medical Technology Data Management Center to ensure concealment. For the purpose of the statistical analysis, the JYKL intervention will be considered the exposure. If a serious adverse event occurs and the patient needs to be rescued, making it is necessary to know the drug used by the patient, the person in charge of each center shall decide to open the blindness and open the corresponding emergency letter. As soon as the corresponding numbered emergency letter is opened, the case will not be included in the study.

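### The named group tests adjust for neither the randomisation stratum (apparently centre) nor baseline PASI, so the primary comparisons lose precision; false positives are not inflated

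*Protocol article*

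**What the plan says.** On randomisation, section 2.5.4 states: "This study will use central district stratification and block randomization", and then "Eligible patients will be randomly assigned, in a 1 : 1 ratio, to one of the two groups". Section 2.1 adds "This study will be performed in five centers in China", with competitive enrolment. The stratification wording is not perfectly clear, but centre is the natural reading.

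On the endpoint, section 2.5.1 makes two statements. The first is "The primary outcome is the reduction in the Psoriasis Area Severity Index (PASI) score", with the formula "PASI reduction = (PASI at baseline)–(PASI at week 8 of the treatment period". The second calls the main result the "percentage of patients whose PASI score decreased by more than 75% compared with the baseline at 8 weeks" (PASI-75). Table 2 schedules PASI at screening and at allocation, so a baseline value exists for every randomised patient.

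On analysis, section 2.5.11 assigns tests by type of variable. For qualitative variables: "We will apply the chi-square test to examine the differences between the experimental and control groups for qualitative variables". For quantitative variables it names the t-test "to examine the differences between two groups for normally distributed quantitative variables", with a Satterthwaite correction if variances differ, and the Wilcoxon rank-sum test where normality fails. It also names a generalized linear model for quantitative outcomes measured repeatedly, without listing its terms. Centre and baseline value appear nowhere in the section. Section 2.5.10 foresees a separate statistical analysis plan, which is not shown.

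**The concern.** When patients are randomised in blocks within centres, the arms are balanced within each centre by design. A test that ignores centre still counts the between-centre variation in its standard error, although the design has removed that variation from the treatment comparison. If centres differ in prognosis, the standard error is too large and the test too cautious.

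Baseline PASI raises a different issue. Subtracting baseline is not the same as adjusting for it: a change score fixes the baseline slope at 1, whereas ANCOVA estimates it. Where baseline and week-8 scores are imperfectly correlated, the change score carries extra noise and does not correct properly for chance imbalance at baseline.

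What is at stake is power in a trial with little to spare: with the plan's own response rates, 89 per group gives just under 80%.

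**Working it through.** **1. The plan's own figure.** Inputs from section 2.5.3: PASI-50 rates 55.66% and 35.3%, alpha 0.05 (two-sided, section 2.5.11), power 80%. The unpooled two-proportion formula gives

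n = (1.960 + 0.842)² × (0.5566 × 0.4434 + 0.353 × 0.647) / (0.5566 − 0.353)² = 89.97, or 90 per group.

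The stated 89 is within rounding of this, and 89 × 1.10 = 97.9 gives the stated 98. By the pooled-variance formula (which would ask for 93) power is 78.4% at 89 per group and 82.2% at 98. The calculation is for an unadjusted comparison of PASI-50; it serves here only to anchor sample size and margin.

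**2. PASI reduction: leaving out baseline.** Assume equal variance (set to 1) at baseline and week 8, with correlation ρ. Neither is given in the documents.

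- Var(change) = 2(1 − ρ)
- Var(ANCOVA) = 1 − ρ²
- Ratio change/ANCOVA = 2/(1 + ρ)

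The power columns assume a 0.4 SD effect and 88 per arm (98 × 0.9 = 88.2), with power = Φ(0.4/√(2·Var/88) − 1.96). The last column shows what ANCOVA would reach if the change-score test had exactly 80%: Φ(2.80/√((1 + ρ)/2) − 1.96).

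| ρ | Var(change) | Var(ANCOVA) | Ratio | Power, change | Power, ANCOVA | ANCOVA where change has 80% |
|---|---|---|---|---|---|---|
| 0.3 | 1.40 | 0.91 | 1.54 | 61% | 79% | 93.5% |
| 0.5 | 1.00 | 0.75 | 1.33 | 76% | 87% | 89.9% |
| 0.7 | 0.60 | 0.51 | 1.18 | 93% | 96% | 86.0% |

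Type I error stays at 5% either way, because baseline PASI is not named as a stratification factor.

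**3. PASI reduction: leaving out centre.** If a share f of the variance lies between centres and the arms are balanced within centre, the true type I error of the t-test is 2[1 − Φ(1.96/√(1 − f))]. For f = 0, 5, 10 and 20% this is 5.0, 4.4, 3.9 and 2.8%.

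**4. Responder endpoint: leaving out centre.** Simulation of five equal centres, 18 per arm in each (180 in total), exactly balanced, comparing the plain chi-square with CMH stratified by centre.

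(a) Overall rate 45.5% under the null; 55.66% vs 35.3% under the alternative; 40,000 runs per setting. Centre effects are assumed on the logit scale.

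| Centre SD (logit) | Null rates across centres | Type I, chi-square | Type I, CMH | Power, chi-square | Power, CMH | Points lost |
|---|---|---|---|---|---|---|
| 0 | 45–45% | 4.7% | 4.7% | 77.8% | 77.9% | 0.1 |
| 0.25 | 37–54% | 4.3% | 4.7% | 77.8% | 78.9% | 1.1 |
| 0.5 | 29–63% | 4.1% | 5.3% | 78.5% | 81.6% | 3.0 |
| 0.75 | 22–70% | 3.3% | 4.9% | 79.4% | 83.6% | 4.3 |
| 1.0 | 16–77% | 2.6% | 4.9% | 80.3% | 86.7% | 6.4 |
| 1.5 | 8–86% | 1.5% | 5.2% | 82.2% | 92.1% | 9.9 |

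(b) A lower control rate, as PASI-75 would have: mean 24% (assumed), odds ratio 2.3, which is the plan's PASI-50 odds ratio (0.5566/0.4434)/(0.353/0.647) carried over; 100,000 runs.

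| Control rates across centres | Type I, chi-square | Power, chi-square | Power, CMH | Points lost |
|---|---|---|---|---|
| 18–30% | 4.8% | 72.8% | 73.0% | 0.2 |
| 14–34% | 4.7% | 71.0% | 72.0% | 1.0 |
| 10–38% | 4.4% | 68.0% | 70.4% | 2.4 |
| 5–50% | 3.3% | 56.4% | 64.1% | 7.7 |

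**The case against.** The best defence is that covariates are commonly left to the statistical analysis plan, that this is a condensed article, and that section 2.5.11 also names a generalized linear model. PASI is measured repeatedly, so that model could carry centre and baseline, and the section never ties one test to the primary outcome by name.

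Part of this stands. The analysis plan may well add these terms, and for PASI reduction the analysis is open rather than settled. But the section is not silent: it names specific tests, down to the variance correction. The model is named only for repeated quantitative measures, so it cannot cover PASI-75, for which the only named method is the unstratified chi-square test.

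The sizes can also be challenged. The documents give no centre effect, no correlation, no SD and no effect size on the PASI scale. Control rates from 5% to 50% across centres are an extreme assumption; the top value exceeds the planned overall control rate for the easier PASI-50 endpoint (35.3%). With narrower spreads the loss is 0 to 3 points. That objection stands, which is why ranges are shown.

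A reader might also infer that the plan ignores baseline altogether. It does not: both endpoint definitions are built on baseline PASI. What is missing is adjustment for it as a covariate.

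**Conclusion.** The point holds as one of efficiency. The plan stratifies randomisation, collects baseline PASI, and then names group tests that adjust for neither.

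A reader might conclude that the p-values are invalid or the false-positive risk raised. The documents do not support that. Omitting baseline PASI leaves type I error intact. Omitting centre shifts it only if centres differ in prognosis, and then downwards.

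The firmer loss is on PASI reduction: a variance 1.18 to 1.54 times that of ANCOVA for correlations from 0.7 down to 0.3, given equal variances at baseline and week 8. For the responder endpoint the loss depends on an unknown centre effect: 0 to 3 points of power with type I error about 4.1% to 4.8% for small to moderate differences, and 6 to 10 points with about 1.5% to 3.3% for very large ones. These runs assume equal centre sizes and exact balance within centre; competitive enrolment may depart from both. Reading the stratification factor as centre is itself an interpretation. The change is worth making because it costs almost nothing, but the plan is not unsound without it.

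**What to change.** State in section 2.5.11, and carry into the analysis plan:

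- PASI reduction at week 8 is analysed by ANCOVA with treatment, centre and baseline PASI, regardless of the normality check, with a rank-based or robust-standard-error sensitivity analysis.
- PASI-75 at week 8 is analysed by a CMH test stratified by centre, or by logistic regression with treatment, centre and baseline PASI. One of the two is named in advance as primary.
- Section 2.5.4 says in plain words that the stratification factor is the study centre, if that is what is meant.

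Centre and baseline PASI are already recorded, so no new data are needed. The cost is a few sentences of analysis wording and a few lines of SAS, fixed before unblinding.

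### The test and effect measure for week-8 PASI reduction depend on the observed distribution, and the role of the repeated-measures model is left open

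*Protocol article*

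**What the plan says.** Section 2.5.1 states: "The primary outcome is the reduction in the Psoriasis Area Severity Index (PASI) score". It is computed as baseline minus week 8, so each patient contributes one quantitative value. The same section adds: "The PASI score of the patients will be assessed every 2 weeks during the treatment period", with further assessments every 4 weeks in follow-up. It also says: "The main result of the RCT will be the percentage of patients whose PASI score decreased by more than 75" percent from baseline at 8 weeks, which is a binary endpoint.

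Section 2.5.11 does not name an analysis for PASI reduction. It gives rules by type of variable:

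- Qualitative variables: chi-square test.
- Quantitative and normal: the t-test "to examine the differences between two groups for normally distributed quantitative variables", with a further step: "the homogeneity of variance will be tested between groups, and the Satterthwaite approximation will be used to correct the variance when the variance is uneven".
- Quantitative and not normal: "and the Wilcoxon rank-sum test for nonnormally distributed quantitative variables".
- Repeated measures: "A generalized linear model will be applied for quantitative variables with repeated measures".

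The descriptive summary follows the same split: mean and SD if normal, median and quartiles if not. Significance is two-sided at 0.05.

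**The concern.** The choice between t-test and rank-sum is made from the outcome data, and no criterion for normality is given. The two do not answer the same question. The t-test compares mean reduction in PASI points at week 8. The rank-sum test compares how the two arms' values rank against each other and does not test the mean. A repeated-measures model may use all visits and so target a third quantity. The article does not say which of these decides for PASI reduction.

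What is at stake is the meaning of the primary result. A reader of the plan cannot say what effect will be estimated or in what units. Where the analyses disagree on significance, the plan gives no ranking to settle the conclusion.

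**Working it through.** **Inputs from the article.** 89 analysable patients per arm (section 2.5.3), 1:1 allocation (2.5.4), two-sided 0.05 (2.5.11), four two-weekly treatment visits (2.5.1). The 89 comes from PASI-50 rates of 55.66% and 35.3% at 80% power. The unpooled normal formula gives (1.960 + 0.842)² × (0.5566 × 0.4434 + 0.353 × 0.647) / 0.2036² = 89.97, within one patient of the stated figure. With 10% added, 89 × 1.10 = 97.9, or 98. This number rests on proportions and is unaffected by the point here; it serves only as the arm size.

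**Inputs that are assumed.** The article gives no PASI mean, SD, shape or between-visit correlation. Two sets were used.

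- Set A, 10,000 runs, no effect. Near-normal version: baseline normal, mean 7, SD 2.5. Right-skewed version: baseline lognormal (log-mean 1.8, log-SD 0.5), fractional reduction beta(2, 2.5). Monte Carlo error is √(0.05 × 0.95 / 10,000), about 0.2 points.
- Set B, 3,000 to 4,000 runs per setting. Baseline gamma, mean 5, SD 3.2; proportional reduction with SD 0.35, bounded between -50% and 100%; between-visit correlation 0.6. Where several figures are given, they come from separate runs, some of which also assumed a mean control reduction of 35% and linear improvement over visits.

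The repeated-measures model was represented by the average reduction over the treatment visits.

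**1. Type I error of the rule as written** (normality check, then t-test or rank-sum): 4.5% near-normal and 5.1% skewed in set A; 5.1% in set B. It is held.

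**2. Type I error if the analyst may choose.** Either t-test or rank-sum: 5.4% and 6.9% in set A; 6.6% to 7.0% in set B. Rule-selected test or visit average: 6.7% and 7.6% in set A. Any of all three: 8.6% to 10.3% in set B.

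**3. How far the effect measure is open.** In set A, Shapiro-Wilk passed both arms in 90% of near-normal trials and in none of the skewed ones. The reported measure would therefore switch to ranks in about 10% of trials in the first case and in all of them in the second. In set B, two common normality checks (Shapiro-Wilk and an uncorrected Kolmogorov-Smirnov) reached different verdicts in about 12-13% of trials, so the unstated criterion matters too.

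**4. Disagreement when there is an effect** (set B). With a 16-point gain in proportional reduction, t-test and rank-sum differ on significance in about 15-16% of trials. The three analyses are not unanimous in about 33-35%.

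**5. Different hypotheses.** In a constructed case with equal mean reduction (1.75 points) but different shapes (35% of one arm nearly clear and the rest almost unchanged, against uniform partial improvement), rank-sum rejects in 51.1% of trials and the unequal-variance t-test in 4.9%. This shows that the targets differ; it is not a forecast for this trial.

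**6. The variance pretest** ("the homogeneity of variance will be tested between groups"). With n per arm equal, the pooled standard error is √[((s₁² + s₂²)/2) × (2/n)] = √[(s₁² + s₂²)/n], which is the Satterthwaite standard error. The t statistic is the same and only the degrees of freedom change, between 88 and 176 at n = 89, so the critical value lies between about 1.99 and 1.97. The pretest gains nothing.

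**7. Power of fixed alternatives** (set B, 16-point effect). Unadjusted unequal-variance t-test about 57%, rank-sum about 65%, mean difference adjusted for baseline PASI about 72%.

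**The case against.** A reader might infer that the plan fails to hold the 5% error rate. The text does not support that. Section 2.5.11 makes t-test and rank-sum mutually exclusive and does not permit reporting whichever is significant; the figures of 7-10% describe a freedom that the article never grants. This objection stands.

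A reader might also infer that the trial's deciding p-value is what floats. That too goes beyond the text. Section 2.5.1 calls the response rate above 75% the main result, and section 2.5.3 sizes the trial on PASI-50. Both are binary and would go to a chi-square test with no pretest. The rule criticised here governs the deciding p-value only if PASI reduction is the deciding endpoint.

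Third, the week-8 reduction is one number per patient, so the repeated-measures sentence can be read as covering the PASI course over visits, not as a rival test. That is a fair reading, but nothing in the article states it or ranks the two.

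Fourth, section 2.5.10 says that a statistician will write an analysis plan, and naming a primary model is often left there. This has force for model detail. It does not cover the data-dependent rule, which the article states itself.

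Finally, on strongly skewed data the rule would almost always select rank-sum, so the disagreement between the two tests would matter less in practice. That holds only if the data are in fact strongly skewed, and the plan does not commit to that.

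**Conclusion.** The point holds as a defect of definition. For PASI reduction, the article lets the observed distribution decide between a mean difference and a rank-based comparison, gives no normality criterion, and leaves the role of the repeated-measures model unstated. Type I error is not the problem when the rule is followed mechanically: it stays near 5%. It would rise to roughly 7-10% only with a free choice among the applicable tests. With a moderate true effect, the analyses would not all agree on significance in about a third of trials.

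The simulated sizes rest on assumed PASI distributions and correlations. The overlap in the rules, and the difference in what they estimate, do not. The change should be made, but it does not by itself settle which endpoint decides the trial.

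**What to change.** In section 2.5.11, or in the analysis plan before unblinding, name one deciding analysis for week-8 PASI reduction that depends on no normality or variance test. Preferred: the between-group difference in mean reduction with 95% CI, from a linear model adjusted for baseline PASI and the centre stratification described in section 2.5.4, with robust standard errors. Make rank-sum a sensitivity analysis and the repeated-measures model supportive. Drop the variance pretest. Use the same pretest-free rule for the other quantitative outcomes (BSA, VAS, DLQI, QOL and the CM syndrome score). Separately, state in section 2.5.1 whether PASI reduction or the response rate above 75% decides the trial.

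Cost: one paragraph of wording, with no new patients or data. The downside is reliance on a mean difference when the data may be skewed. An unadjusted mean comparison would give up power to rank-sum under the assumptions above (57% against 65%); adjusting for the baseline PASI already collected more than recovers it (72%). If the sponsor prefers rank-sum with a Hodges-Lehmann estimate, naming it now would also resolve the point, at the price of giving up the mean difference.
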